#### Assessment of treatment fidelity

3.7.2

Treatment fidelity will be assessed by a self-report questionnaire administered to study interventionists following completion of the study session. The study team elected not to record study sessions for fidelity monitoring due to the concerns regarding participant reactions to recordings in the setting of a trial focused on PTSD (characterized in part by hyperarousal, paranoia) and the sensitivities associated with discussing firearm storage practices.

### Safety protocol

3.8

The study will be monitored by a Data and Safety Monitoring Board (DSMB). The DSMB includes four individuals with expertise spanning suicide prevention, firearm safety, PTSD, clinical trials methodology, and biostatistics. The DSMB will meet after the first 20 to 30 patients have been enrolled in the study, with subsequent meetings occurring every six months. If the DSMB or the investigator team determines that the risks of participating outweigh any potential benefits, the study may be discontinued.

Because all study procedures will take place virtually, including the intervention being delivered over the HIPAA-compliant Zoom platform, study staff will ensure that they have the participant's current location at the beginning of the consent visit and the intervention visit. Study staff will monitor for adverse events (AEs) and serious adverse events (SAEs), which will be reported to the IRB and DSMB according to standard practices. This trial is not specifically recruiting individuals with current or past suicidal symptoms (e.g., suicidal ideation, suicide attempts). However, as noted, all participants will complete the CRP intervention. We will follow standard clinical procedures if a participant were to report suicidal symptoms necessitating intervention (e.g., emergency rescue). We will also provide participants with a resource guide that lists information for national and local emergency services, crisis hotlines, a national map for out-of-home firearm storage and locations for purchase of locking devices.

### Data collection and analysis

3.9

#### Statistical analysis for primary outcome

3.9.1

The primary endpoint will be analyzed using a generalized linear mixed model (GLMM) with a logit link with a random intercept per participant (Hypothesis 1a). The actual firearm storage practice score at the 6-month follow-up assessment is a continuous value from 0 to 4. The primary outcome is the improvement from baseline, which is a binary transformation of the score. It measures whether the difference between the 6-month and baseline scores is >0. If the score difference exceeds 0, the transformed primary outcome is 1 (and 0 otherwise). We will model the primary outcome (improvement at 6 months) using a GLMM with a logit link, incorporating longitudinal information from all follow-up time points. This model accounts for the missingness of measurements at follow-up time points. Similar to the 6-month score, we will include dichotomized scores from post-intervention, 1-month, and 3-month measures in the GLMM with a random intercept representing each participant. The treatment effect of PSG-T will be compared between the two arms, with terms for intervention arm, baseline firearm storage practice scores, interaction between intervention and the follow-up time points, interaction between baseline score and follow-up time, and other covariates specified *a priori*. This model formulation was found to have the least amount of bias when baseline measures were subtracted from follow-up measures and patients had differential missingness of follow-up measures between intervention and control groups [45]. There are no interim analyses planned.

#### Statistical analysis for secondary outcomes

3.9.2

Secondary endpoints include evaluating the efficacy of PSG-T compared with PSG on knowledge about the link between firearm storage practices and suicide risk and intentions to store firearms securely (Hypothesis 1b and 1c). We will use GLMM with an appropriate link function and a random intercept per participant to model the between- and within-group differences of outcomes over time [46]. For secondary outcomes reported in Likert scales, we will conduct sensitivity analysis by treating them as ordinal outcomes in the cumulative logit mixed model. To prevent model convergence issues in the cumulative logit model, we will assess the distribution of the ordinal by each category's relative proportions and pre-specify whether we will analyze the raw scale or merged category scores. We will use causal mediation analysis to evaluate PTSD-related negative cognitions about the world as a potential mechanism of change in PSG-T for increasing knowledge, intentions, and behaviors regarding safe firearm storage practices (Hypothesis 2) [47].

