## Abstract

Firearm injury is the most common suicide method. When firearms are stored in a non-secure manner (e.g., unlocked, loaded), risk for suicide may be elevated. Accordingly, clinical, public health, and firearm industry stakeholders recommend efforts to promote secure firearm storage, such as lethal means safety counseling (LMSC). One LMSC intervention, Project Safe Guard (PSG), has demonstrated efficacy in prompting use of firearm locking devices in a sample of military service members; however, subsequent analyses show that PSG has diminished efficacy for individuals with elevated symptoms of posttraumatic stress disorder (PTSD). PTSD, characterized in part by hypervigilance to threat, is associated with elevated suicide risk as well as a greater likelihood of storing firearms using less secure methods. In response, our group developed an adaptation of PSG, termed Project Safe Guard-Trauma (PSG-T). This paper describes the design, methodology, and protocol of a randomized controlled trial comparing PSG-T to PSG among adults who screen positive for PTSD related to a victimization trauma (e.g., physical assault, sexual assault, combat) and who do not currently store all their personally owned firearms in a secure manner. PSG and PSG-T will be delivered by licensed clinical psychologists. Assessments will occur at pre-intervention, post-intervention, and 1-, 3-, and 6-month follow-up. The primary objective is to determine the efficacy of PSG-T in prompting greater beliefs and practices regarding secure storage of personal firearms.

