## Research aim and hypotheses

2

This study has two aims and related hypotheses. Aim 1 is to conduct a two-armed RCT to evaluate the efficacy of PSG-T compared with a control (the PSG intervention that does not focus on PTSD) in increasing knowledge about the link between firearm storage practices and suicide risk, intentions to store firearms securely, and secure firearm storage behaviors. Hypothesis 1 is that compared with control, at 1-, 3-, and 6-month follow-up, PSG-T will result in greater (a) adoption of secure firearm storage practices (primary outcome at 6-month follow-up), (b) knowledge about the link between firearm storage practices and suicide risk, and (c) intentions to store firearms securely.

Aim 2 is to evaluate differences in PTSD-related negative cognitions about the world as a potential mechanism of change in PSG-T for increasing knowledge, intentions, and behaviors regarding secure firearm storage practices. Hypothesis 2 is that participants who receive PSG-T will report fewer PTSD-related negative cognitions about the world compared with participants who receive PSG, and these decreases will be associated with increases in (a) adoption of secure firearm storage practices (b) knowledge about the link between firearm storage practices and suicide risk, and (c) intentions to store firearms securely.

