#### Model covariates, diagnostics, and interpretation

3.9.3

Covariates will be included in the multivariate analysis if they are associated with missingness or be determined to be adjusted for *a priori*. Continuous outcomes will be transformed if normality assumptions are violated. Goodness of fit statistics will be calculated and model fitting diagnostics will be assessed to examine influential points, outliers, and heteroscedasticity. There is a single primary endpoint, and no adjustment will be made for multiple comparisons concerning secondary endpoints and analyses; appropriate caution will therefore be used in interpreting the results of hypothesis testing for these analyses.

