#### Power

3.9.5

This study is powered according to the standardized effect size, Cohen's h, of the primary endpoint without considering correlations between longitudinal measures, which will provide a larger (more conservative) sample size estimate than if the study was powered based on the longitudinal correlation estimate in a GLMM [51]. Cohen's h is the standardized effect size for the between-group difference in proportions and is not affected by control group proportions [51,52]. Based on our preliminary result of the proportion of new uses of firearm locking devices in the intervention group (PSG-T, 30% = 55%–25%) and the control group (11.5% = 39%–27.5%), we calculated a Cohen's h of 0.47. A sample size of 150 (75 in each group) produces 80% power (α = 0.05) to detect a Cohen's h of 0.47 in measuring the between-group differences of proportions of reported new secure firearm storage behaviors. The proposed sample size of *N* = 168 participants (84 in each group) allows us to have >80% statistical power for the primary analysis and will yield 80% power to detect any subgroup-specific effect or standardized secondary outcomes of 0.47 or greater between PSG-T and control. The power will be at least 60% if the standardized subgroup-specific effect size is at least 0.35.

We used Monte Carlo simulation with 1000 replications to assess the power of *N* = 168 for the secondary outcomes, namely the mediation analysis of the PTSD-World in the PSG-T effect to increase knowledge, intentions, and behaviors regarding safe firearm storage practices [53]. Assuming the outcome standard deviation is 0.5, direct effect of PSG-T on PTSD is 0.6 and direct effect of PTSD on outcomes is 0.5, and the standard deviation is 1.3 for PTSD-World from Sexton et al. [54], a sample size of 168 allows us to detect a mediation effect of 0.30 (in Cohen's h scale) with 86 % power (α = 0.05).

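### Knowledge and intentions are modelled with a random intercept alone; on an identity link this assumes equal variance and correlation at all visits, and baseline-referenced 6-month standard errors are likely too small if correlation decays

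*Protocol article*

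**What the plan says.** Section 3.9.2 of the protocol article names the model for the secondary outcomes: "GLMM with an appropriate link function and a random intercept per participant to model the between- and within-group differences of outcomes over time". It mentions no random slope, residual correlation structure or robust standard error. For Likert-type outcomes it adds that "we will conduct sensitivity analysis by treating them as ordinal outcomes in the cumulative logit mixed model".

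The visits are unevenly spaced: "Assessments will occur at pre-intervention, post-intervention, and 1-, 3-, and 6-month follow-up" (Abstract). Table 2 schedules both knowledge and intentions at all five. Section 2 states the hypothesis at three of them: "compared with control, at 1-, 3-, and 6-month follow-up, PSG-T will result in greater" storage adoption, knowledge and intentions. Only storage adoption has 6 months as its primary time point.

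Section 3.9.3 plans that "Continuous outcomes will be transformed if normality assumptions are violated" and that "model fitting diagnostics will be assessed to examine influential points, outliers, and heteroscedasticity", without saying what follows if a check fails. It also says that "no adjustment will be made for multiple comparisons concerning secondary endpoints and analyses".

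**The concern.** On an identity link, a random intercept with independent residuals is compound symmetry: every visit has the same variance and every pair of visits the same correlation. Here the pre- and post-intervention assessments lie around a single session, while the last visit is six months later. Scores taken around one session would ordinarily correlate more strongly than scores six months apart.

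If they do, the model applies one average correlation to all contrasts. A contrast that uses baseline then gets a standard error that is too large where the true correlation with baseline is high (post-intervention, 1 month) and too small where it is low (6 months). At 6 months the nominal 5% test would reject too often and confidence intervals would be too narrow; at the early visits power would be lost. Putting baseline in as a covariate does not remove this, because the variance left after adjustment still differs by visit.

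**Working it through.** **The plan's own figures.** The article gives no standard error, visit-specific standard deviation (SD) or between-visit correlation for knowledge or intentions, so there is no stated figure to reproduce. The sample size in section 3.9.5 does reproduce (30% against 11.5% by the two-proportion formula gives 75 per arm, power 0.804), but it concerns the primary endpoint and does not bear on this point. The ratios below do not depend on sample size.

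**Inputs.** From the article: five visits, random intercept only, two arms, α = 0.05 (taken as two-sided). Assumed: identity link, complete data, free arm-by-visit means, model-based standard errors, and all SDs and correlations.

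**Formulas.** Let V be the true 5 × 5 covariance matrix, index 0 be baseline, v̄ the mean of the five variances and c̄ the mean of the ten covariances. The random-intercept fit works with v̄ and c̄. The ratio of model to true standard error at visit k is:
- raw arm difference: √(v̄ / V_kk)
- change from baseline: √[2(v̄ − c̄) / (V_00 + V_kk − 2V_0k)]
- baseline-adjusted (baseline-by-visit slopes): √(mean of R_j over the four follow-ups / R_k), where R_k = V_kk − V_0k²/V_00

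Actual α = 2[1 − Φ(1.96 × ratio)].

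**Worked case: SD 1 throughout, correlation 0.80 falling to 0.60.** Take ρ(d) = 0.80 × (0.60/0.80)^(d/6) for d months apart, with post-intervention at d = 0 from baseline. From baseline this gives 0.80, 0.7625, 0.6928 and 0.60; post-intervention has the same values with 1, 3 and 6 months. The other pairs are 0.7268 (1–3), 0.6295 (1–6) and 0.6928 (3–6). The ten values average c̄ = 0.696.
- Raw difference: √(1/1) = 1.00 at every visit.
- Change at 6 months: √[2(1 − 0.696)/(2 − 1.20)] = √(0.608/0.80) = 0.87, α = 8.8%.
- Baseline-adjusted: R = 0.36, 0.4186, 0.52, 0.64, mean 0.485. At 6 months √(0.485/0.64) = 0.87, α = 8.8%. At post-intervention √(0.485/0.36) = 1.16.

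**Same formulas, other decay patterns (equal SDs; change / baseline-adjusted):**

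| Correlation pre–post to pre–6 months | Ratio at post | Ratio at 1 month | Ratio at 6 months | α at 6 months |
|---|---|---|---|---|
| 0.70 to 0.60 | 1.08 / 1.05 | 1.05 / 1.03 | 0.94 / 0.94 | 6.6% / 6.5% |
| 0.80 to 0.60 | 1.23 / 1.16 | 1.13 / 1.08 | 0.87 / 0.87 | 8.8% / 8.8% |
| 0.85 to 0.55 | 1.44 / 1.30 | 1.22 / 1.12 | 0.83 / 0.82 | 10.4% / 10.7% |
| 0.90 to 0.50 | 1.78 / 1.55 | 1.31 / 1.17 | 0.80 / 0.78 | 11.9% / 12.6% |

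Simulation of the last three patterns (3,000 trials each, 75 per arm) gave 8.6% / 8.1%, 10.5% / 12.0% and 12.9% / 13.6%, in line with the formulas.

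**Changing the SDs.**
- Constant correlation 0.6, equal SDs: all ratios are 1.00 and α is 5.0%.
- Constant correlation 0.6, SD falling as 1, 1, 0.95, 0.85, 0.75: v̄ = 4.1875/5 = 0.8375. Raw difference at 6 months √(0.8375/0.5625) = 1.22, α = 1.7%; baseline-adjusted √(0.7969/0.5625) = 1.19, α = 2.0%. The direction reverses.
- Correlation 0.80 to 0.60 with the same falling SDs: R = 0.36, 0.378, 0.376, 0.36, mean 0.368; baseline-adjusted ratio √(0.368/0.36) = 1.01, α = 4.7%. For change, c̄ = 0.580 and √[2(0.8375 − 0.5804)/(1.5625 − 0.90)] = 0.88, α = 8.4%.
- Constant correlation 0.6, SD rising as 1, 1, 1.05, 1.15, 1.3: raw difference √(1.223/1.69) = 0.85, α = 9.5%.

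**The case against.** Most of the case on the other side stands as a limit on the claim.

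- A reader might infer that the 6-month standard error is too small as a matter of fact, with a false-positive rate about double 5%. The article does not support that. It gives no SDs or correlations, and a falling SD, which is plausible if scores approach a ceiling, can cancel or reverse the effect.
- The contrast is not fixed. Section 2 can be read as a plain arm difference at each visit. With complete data, unequal correlation alone leaves that contrast's standard error correct; only unequal variances disturb it. Against this, section 3.9.2 also sets out to model differences within groups, and the primary model in section 3.9.1 conditions on baseline, so baseline-referenced contrasts are likely.
- The link is open, and section 3.4.3 gives no scoring for the knowledge questionnaire. On a logit or cumulative logit link the constraint is on the latent scale, and nothing here shows a fault there. The one non-identity result available, a simulation of the primary binary model, rejected 4.8% of the time. Extending the point to that model, or asking for robust standard errors on other links, would go too far.
- Covariance structure is often left to the analysis plan. But the article does not leave it open: it names the random intercept, and an analysis plan that follows the text would carry it forward.
- Diagnostics are planned. They name no remedy, and a heteroscedasticity check does not look for unequal correlations.
- Secondary results are to be read with caution. That caution concerns multiplicity; it does not make a single nominal 5% test or interval valid.

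**Conclusion.** The point holds conditionally. If knowledge or intentions is analysed as a score on an identity link, if the contrast uses baseline, and if correlation with baseline falls over time, the random-intercept model likely understates the 6-month standard error and overstates the early ones. With equal SDs and the four decay patterns tabulated, the 6-month standard error is about 6% to 22% too small and two-sided type I error about 6.5% to 13%. These sizes rest on assumed correlations and are not estimates for this trial. Flat correlation with constant SD gives no error.

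The reason to change is that the stated structure makes validity depend on a pattern that nobody has yet seen and that the visit schedule makes unlikely. The point affects unadjusted secondary endpoints only and is of low severity. The primary conclusion of the trial is untouched.

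**What to change.** In section 3.9.2, or in the analysis plan that implements it, state that secondary scores analysed on an identity link will be fitted with an unstructured within-participant covariance across visits in place of the random intercept, by REML, with Kenward-Roger or Satterthwaite degrees of freedom. Name the fallback in advance, for example heterogeneous Toeplitz, if the model does not converge. That fallback ties correlations by number of visits apart and not by months, so it is second best, but it still frees the variances and lets correlation decay.

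No change is needed for other links, for the cumulative logit sensitivity analysis or for the primary binary model.

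The cost is wording. With baseline as a response there are 5 × 6/2 = 15 covariance parameters, and with baseline as a covariate 4 × 5/2 = 10, against 2 for the random intercept, with 168 participants planned. The downside is occasional non-convergence, which the fallback covers. If the correlation proves flat, little is lost.

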#### Model covariates, diagnostics, and interpretation

3.9.3

Covariates will be included in the multivariate analysis if they are associated with missingness or be determined to be adjusted for *a priori*. Continuous outcomes will be transformed if normality assumptions are violated. Goodness of fit statistics will be calculated and model fitting diagnostics will be assessed to examine influential points, outliers, and heteroscedasticity. There is a single primary endpoint, and no adjustment will be made for multiple comparisons concerning secondary endpoints and analyses; appropriate caution will therefore be used in interpreting the results of hypothesis testing for these analyses.

#### Missing data

3.9.4

We expect minimal missingness (at most 10%) for the primary outcome at 6-month follow up, based on prior successes recruiting and retaining participants who report firearm ownership, and/or PTSD symptoms and the low missingness rate in prior related studies at 6-month follow-up [17,48]. Before the final analysis, missing data patterns will be assessed to determine if missingness is random/ignorable [49,50]. The logistic regression use in the primary analysis will use all available data and will adjust for covariates associated with missingness. Multiple imputation with chained equations for imputing outcomes missing at random will be considered. Patten-mixture models or sensitivity analysis will be considered if outcomes are not missing at random.

#### Power

3.9.5

This study is powered according to the standardized effect size, Cohen's h, of the primary endpoint without considering correlations between longitudinal measures, which will provide a larger (more conservative) sample size estimate than if the study was powered based on the longitudinal correlation estimate in a GLMM [51]. Cohen's h is the standardized effect size for the between-group difference in proportions and is not affected by control group proportions [51,52]. Based on our preliminary result of the proportion of new uses of firearm locking devices in the intervention group (PSG-T, 30% = 55%–25%) and the control group (11.5% = 39%–27.5%), we calculated a Cohen's h of 0.47. A sample size of 150 (75 in each group) produces 80% power (α = 0.05) to detect a Cohen's h of 0.47 in measuring the between-group differences of proportions of reported new secure firearm storage behaviors. The proposed sample size of *N* = 168 participants (84 in each group) allows us to have >80% statistical power for the primary analysis and will yield 80% power to detect any subgroup-specific effect or standardized secondary outcomes of 0.47 or greater between PSG-T and control. The power will be at least 60% if the standardized subgroup-specific effect size is at least 0.35.

We used Monte Carlo simulation with 1000 replications to assess the power of *N* = 168 for the secondary outcomes, namely the mediation analysis of the PTSD-World in the PSG-T effect to increase knowledge, intentions, and behaviors regarding safe firearm storage practices [53]. Assuming the outcome standard deviation is 0.5, direct effect of PSG-T on PTSD is 0.6 and direct effect of PTSD on outcomes is 0.5, and the standard deviation is 1.3 for PTSD-World from Sexton et al. [54], a sample size of 168 allows us to detect a mediation effect of 0.30 (in Cohen's h scale) with 86 % power (α = 0.05).

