Project Safe Guard (PSG) is a LMSC intervention delivered through a brief interaction that uses motivational interviewing (MI) principles to encourage behavior change [17]. A randomized controlled trial (RCT) compared the efficacy of PSG, either alone or in combination with the provision of firearm cable locks, in prompting secure storage practices compared to a health counseling control among 232 firearm-owning military service members [17]. At 6-month follow-up, PSG outperformed the control intervention in prompting new use of locking devices (55.0 % vs. 39.0 %; OR = 1.91, 95 % CI = 1.10–3.32), and the combination of PSG and cable lock provision was not superior to either intervention alone. However, a secondary analysis of the PSG RCT found that the intervention-related benefits were attenuated for participants with elevated posttraumatic stress disorder (PTSD) symptoms [18]. This is especially concerning considering research demonstrating that individuals with PTSD are significantly more likely than individuals without PTSD to think about, attempt, and die by suicide [[19], [20], [21], [22]].

There are multiple reasons why the efficacy of safety interventions, such as PSG, may have differential impacts on patients with PTSD. PTSD affects safety perceptions and firearm storage practices (Fig. 1) [23]. PTSD is characterized by symptoms that have their onset or worsen following exposure to a traumatic event, persist for at least one month, and cause clinically significant distress or impairment [24]. The core symptoms of PTSD span four primary domains—intrusions, avoidance, negative alterations in cognitions and mood (e.g., beliefs that the world is unsafe), and marked alterations in arousal and reactivity/hyperarousal (e.g., being “on guard” for potential dangers). Individuals with PTSD, versus those without PTSD, report stronger beliefs that firearms protect from victimization [25], and individuals who report protection from others as a primary reason for firearm ownership, versus those who do not, are more likely than others to store their firearms non-securely [23,[26], [27], [28]]. In a sample of 327 firearm-owning military service members, elevated levels of PTSD hyperarousal symptoms were associated with increased odds of storing a firearm loaded and in a non-secure location [29].

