#### Firearm ownership and storage beliefs and practices

3.4.2

Participants will complete a comprehensive self-report measure of their firearm storage practices, including current use of firearm locking devices (both keyed and biometric devices), reasons for using or not using a locking device, likeliness that participant will encounter a situation that requires use of firearm, and likeliness to adhere to clinician's secure storage recommendations.

The primary outcome will be assessed by asking participants, “Thinking about the firearms in or around your home that you personally own, do you store them using any of the following methods?” Participants will be presented with two methods: “unloaded” and “locked.” For each method, they will be asked to indicate *Yes, all of my firearms*, *Yes, some of my firearms*, or *No, none of my firearms*. We assign a score of 2 if the secure practice applies to all firearms, 1 if it applies to some firearms, and 0 if it applies to none. A higher score corresponds to more secure storage practices. The maximum score, achieved when all firearms are both unloaded and locked, is 4, while the minimum score is 0. Improvement will be defined as a change score >0 between the pre-intervention and 6-month follow-up assessments.

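### The planning effect h = 0.47 comes from subtracting 25% and 27.5% from figures that the Introduction already reports as new lock use, so 0.47 is unsupported as the expected effect until the two sections are reconciled

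*Protocol article*

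**What the plan says.** The Introduction, describing the earlier randomized trial in 232 firearm-owning service members, says that "PSG outperformed the control intervention in prompting new use of locking devices" at 6 months: 55.0% vs 39.0%, OR 1.91, 95% CI 1.10–3.32. The comparator there was health counseling.

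Section 3.9.5 (Power) starts from the "proportion of new uses of firearm locking devices in the intervention group (PSG-T, 30% = 55%–25" per cent) and from 11.5% (39% minus 27.5%) in the control group. From these, "we calculated a Cohen's h of 0.47". It continues: "A sample size of 150 (75 in each group) produces 80% power (α = 0.05) to detect a Cohen's h of 0.47", and says that 168 participants (84 per arm) "allows us to have >80% statistical power for the primary analysis". It does not say what 25% and 27.5% are.

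Section 3.4.2 fixes the endpoint being powered: "Improvement will be defined as a change score >0 between the pre-intervention and 6-month follow-up assessments". The score runs from 0 to 4 and combines an unloaded item and a locked item, each rated none, some or all.

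**The concern.** The same two percentages serve as the new-use proportions in one section and as the starting point for deriving the new-use proportions in another. At most one of these can be right. The pair chosen matters, because the subtraction widens the planned difference from 16 to 18.5 percentage points and moves both rates to a part of the scale where a given difference yields a larger h.

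Two mismatches add to this. The 55% arm is labelled PSG-T in the Power section, while in the Introduction it is PSG, which is the control in the present trial. And the rates concern locking devices only, while the endpoint also counts gains on the unloaded item.

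This effect size is the only stated basis for N = 150 and 168. If it is wrong, readers and the funder hold a mistaken view of what the trial can show, and a null result would be hard to interpret.

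**Working it through.** **Inputs.** 55%, 39%, 25%, 27.5%, h = 0.47, α = 0.05, 75 and 84 per arm (section 3.9.5); at most 10% missing at 6 months (section 3.9.4), so 84 × 0.9 = 75.6 evaluable per arm; OR 1.91 (Introduction). Sidedness is not stated. I take it as two-sided, because a one-sided test at h = 0.47 would need only about 56 per arm and does not reproduce 75.

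**Formulas.** h = 2·asin(√p₁) − 2·asin(√p₂); power = Φ(h·√(n/2) − 1.96); n per arm for 80% power = 2·(2.802/h)².

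**1. The plan's own figure.** For 30% vs 11.5%, h = 1.159 − 0.692 = 0.467, which matches 0.47. The arcsine formula gives 2·(2.802/0.467)² ≈ 72 per arm; the pooled two-proportion formula gives exactly 75. Then 75/0.9 = 83.3, rounded up to 84, or 168 in total. The step from the two rates to N is sound.

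**2. Reading A: 55% and 39% are new use, as the Introduction says.** No subtraction applies.
- h = 1.671 − 1.349 = 0.322.
- Power at 84 per arm: Φ(0.322 × √42 − 1.96) = Φ(0.127) = 0.55.
- Power at 75.6 per arm: Φ(0.322 × √37.8 − 1.96) = Φ(0.020) = 0.51.
- For 80% power: 151.4, so 152 evaluable per arm.

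**3. Reading B: 55% and 39% are total use at 6 months, and 25% and 27.5% are use at baseline.** Use at 6 months = baseline use + gains − losses, so 30% and 11.5% are gains minus losses. They equal the share of the sample who newly adopt only if nobody reverts. Even then the denominator includes people already using locks. Restricting to baseline non-users:
- intervention 0.30/0.75 = 40.0%; control 0.115/0.725 = 15.9%;
- h = 1.369 − 0.819 = 0.550;
- power: Φ(0.550 × √37.8 − 1.96) = Φ(1.42) = 0.92 and Φ(0.550 × √42 − 1.96) = Φ(1.61) = 0.95.

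**4. What N = 168 can detect.** h at 80% power = 2.802 × √(2/84) = 0.43 with complete data, and 2.802 × √(2/75.6) = 0.46 with 10% missing.

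| Reading | Rates | h | Power, 75.6 per arm | Power, 84 per arm |
|---|---|---|---|---|
| Plan | 30% vs 11.5% | 0.467 | 82% | 86% |
| A: already new use | 55% vs 39% | 0.322 | 51% | 55% |
| B: total use, baseline non-users, no reversion | 40% vs 15.9% | 0.550 | 92% | 95% |

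**The case against.** The calculation itself is correct. Given 30% and 11.5%, h is 0.47, 75 per arm is right, and 168 allows for 10% missingness. The full-sample statement of at least 80% power for h = 0.47 holds whatever the percentages mean, since the detectable h is 0.43–0.46. All of that stands. It leaves open why 0.47 should be expected.

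Four stronger readings are tempting and are not supported:

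- **A reader might infer that the trial's power is 51–55% rather than above 80%.** That follows only under reading A. The article does not show which section is mislabelled, and under reading B power could exceed the stated figure. Nor is 55% vs 39% this trial's contrast: it compares PSG with health counseling in service members, whereas this trial compares PSG-T with PSG in people who screen positive for PTSD. It says nothing direct about this trial's chance of success.
- **A reader might take the odds ratio as proof of reading A.** 55% vs 39% gives (0.55/0.45)/(0.39/0.61) = 1.91, as reported, while 30% vs 11.5% gives 3.30, close to the upper confidence limit of 3.32. But the match shows only which percentages the odds ratio was computed from. It would be 1.91 whether they are new or total use, and setting 3.30 against that interval is like for like only under reading A.
- **A reader might apply OR 1.91 to an 11.5% control rate and arrive at a still smaller effect.** That takes the odds ratio from one reading and the control rate from the other, so it is not a consistent scenario.
- **A reader might conclude that the claim that ignoring the repeated measures gives a "which will provide a larger (more conservative) sample size estimate than if the study was powered based on the longitudinal correlation estimate" is wrong and should go.** The article does not give enough to test this for the planned mixed model, and the claim rests on a cited source not at hand. It is a separate matter, and it does not justify 0.47 either.

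Two inferences on my side should also be plain. The article never calls 25% and 27.5% baseline rates, though that is the natural guess. And the Power section refers only to a preliminary result, so its identity with the earlier trial is inferred from the matching percentages and outcome.

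**Conclusion.** The inconsistency between the Introduction and section 3.9.5 is real, and neither reading supports the derivation of 0.47. Under the Introduction's label there is nothing to subtract, h is 0.32, and power at that effect is about 51–55%. Under the other label the Introduction is wrong, and 30% and 11.5% are net changes in lock use rather than the individual improvement that section 3.4.2 defines; h is then about 0.55 if nobody reverts and only baseline non-users are counted.

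That denominator is itself only an approximation. The trial excludes only people who already store every firearm unloaded and locked, so some participants will use locks at baseline, and gains on the unloaded item count as well.

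The conclusion is therefore that 0.47 is unsupported as the expected effect, not that the trial is shown to be underpowered. The figures assume a two-sided 5% test, equal arms and a simple comparison of two proportions, which is the basis the plan itself uses.

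**What to change.** - State in both places what 55%, 39%, 25% and 27.5% are: new use or total use, at which time, in which trial and in which arms. Correct the PSG-T label if the 55% is the earlier PSG result.
- Where the earlier data allow, recompute h from individual-level improvement on the unloaded and locked items among owners who were not fully secure at baseline, and say how far a contrast of PSG with health counseling can stand in for PSG-T with PSG.
- Restate the power. If 55% and 39% are new use, give about 51–55% at h = 0.32 and a detectable h of 0.43–0.46 at 80% power. If they are total use, correct the Introduction and give the basis for the improvement proportions used instead.
- Keep the statement that 168 participants give at least 80% power for h = 0.47 in the full sample, presented as a detectable effect rather than an expected one.

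The cost is a re-analysis of existing data, where available, and a few sentences of text. N, the endpoint, randomization and the analysis model are unaffected. The only downside is that the stated power may become less favourable.
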